### Sample size

In order to ensure that the sample size is adequately powered to estimate a reliable standard deviation (SD) for a phase III trial, Teare et al. has recommended to include at least 70 subjects (35 per arm) for estimating the SD for a continuous outcome [31]. Therefore, to account for a 10% dropout, a total sample size of 80 patients (rounded up from 78), with 40 participants on each arm, is required for this study.

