### Safety monitoring

Safety of study participants will be monitored at every time point assessment through blood tests evaluating organ functions such as liver and renal function tests, electrolyte level and full blood count. Participants will be asked to report any adverse effects experienced during the follow-up period which are graded according to the Common Terminology Criteria for Adverse Events (CTCAE) version 5 [37]. There are five grades in ascending order of severity, with grade 1 representing mild symptoms and grade 5 representing death. In order to monitor the adverse events (AEs) or serious adverse events (SAEs), an independent Data and Safety Monitoring Board (DSMB) review will convene for every 20 patients recruited for the trial. Therefore, there will be a total of three DSMB meetings for this trial. Analysis comparing the incidence of AEs based on the intervention group will be conducted at each DSMB review. The DSMB will make recommendations to the study team regarding the appropriate courses of action to address study safety issues which may arise during the trial. Unblinding to the study team is allowed only when the identification of the intervention arm is absolutely necessary for further management of the participant, for example, in the event of a SAE.

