#### Secondary outcomes

Secondary outcomes are the changes in MFSI-SF and FACT-Cog total scores, including the subscale or domain scores between the XBYRT and placebo arms from baseline to 4, 8 and 10 weeks after baseline. Changes in the functional and symptom domain scoring of the EORTC QLQ-C30 from baseline will also be evaluated. Safety outcomes will be reported as the incidence of AEs or SAEs in study participants.

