### Statistical analysis

The difference in GHS scores at 8 weeks after baseline between XBYRT intervention and placebo will be assessed using independent *t* test. To assess for the longitudinal effect of score changes over time, linear mixed models will be used to compare the outcomes between XBYRT intervention and placebo at the respective time points, adjusting for baseline values and clinically relevant factors. Individual-specific effects will be treated as random effects. Biomarker levels will also be evaluated using *t* tests and linear mixed models. The safety outcomes will be reported in proportions of patients experiencing AEs (% in terms of incidence) using the CTCAE v5.0 Criteria. Chi-square test will be used to evaluate the difference in severity (by grades) between the XBYRT intervention and placebo groups. An intention-to-treat (ITT) analysis approach will be adopted, and the data from all participants who are randomized and completed the trial without any major violation of the protocol will be analysed. Missing data will be treated as missing completely at random.

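### The safety outcome is AE incidence, but the only final between-arm safety comparison named is a chi-square on severity grades, and incidence gets no between-arm estimate or interval

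*Protocol article*

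**What the plan says.** All of this is in the protocol article.

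- **Secondary outcomes** sets the safety outcome: "Safety outcomes will be reported as the incidence of AEs or SAEs in study participants".
- **Statistical analysis** says how it is reported at the end: "The safety outcomes will be reported in proportions of patients experiencing AEs (% in terms of incidence) using the CTCAE v5.0 Criteria". No between-arm difference, interval or test is attached to those proportions.
- The next sentence of **Statistical analysis** names the one final between-arm safety comparison: "Chi-square test will be used to evaluate the difference in severity (by grades) between the XBYRT intervention and placebo groups". It does not say whether the unit is the participant or the event, or whether participants with no AE have a row in the table.
- **Safety monitoring** describes the scale: "There are five grades in ascending order of severity, with grade 1 representing mild symptoms and grade 5 representing death". No grade 0 is mentioned.
- **Safety monitoring** also plans a comparison of incidence during the trial: "Analysis comparing the incidence of AEs based on the intervention group will be conducted at each DSMB review". Reviews follow every 20 patients recruited: "Therefore, there will be a total of three DSMB meetings for this trial".

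**The concern.** The article does more than report safety descriptively. It chooses a between-arm test, and that test is aimed at a different quantity from the outcome it has stated. Incidence asks how many of the randomised participants had an AE. Severity by grade asks how bad the AEs were.

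The two can part company. If the grade table holds only participants who have a grade, it conditions on something that happens after randomisation, and the number of participants affected in each arm drops out of the test. Extra mild AEs in one arm would even make that arm's grade profile look milder. The one p-value printed beside the AE proportions would then concern another quantity, and a reader could take it as the trial's answer on safety. Evaluating safety is one of the trial's declared aims, so the formal comparison should be on the stated outcome.

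**Working it through.** **Inputs from the protocol article.** 40 participants per arm (Sample size); grades 1 to 5 (Safety monitoring); a chi-square on grades (Statistical analysis). The sample size reproduces: 70 / (1 − 0.10) = 77.8, so 78, rounded up to 80. It comes from a requirement of "at least 70 subjects (35 per arm) for estimating the SD for a continuous outcome", so it was not set by any AE rate. The article gives no AE rate, alpha or power for safety.

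**Assumed inputs.** All AE counts and grade mixes below are illustrations, with two-sided alpha 0.05 and one worst grade per participant.

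**Example 1: incidence doubled, same grade mix.** XBYRT 24/40 with an AE (18 grade 1, 4 grade 2, 2 grade 3); placebo 12/40 (9, 2, 1). Pearson chi-square = Σ(O − E)²/E.

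- *Graded participants only.* Both arms have 75%, 16.7% and 8.3% in grades 1 to 3, so O = E in every cell. Chi-square = 0.00, p = 1.00.
- *With a no-AE category* (16/18/4/2 v 28/9/2/1). With equal arms, each E is half the column total: 22, 13.5, 3, 1.5. Chi-square = 2×6²/22 + 2×4.5²/13.5 + 2×1²/3 + 2×0.5²/1.5 = 3.27 + 3.00 + 0.67 + 0.33 = 7.27 on 3 df, p = 0.064.
- *Incidence, 2x2* (24/16 v 12/28). Chi-square = 2×6²/22 + 2×6²/18 = 3.27 + 4.00 = 7.27 on 1 df, p = 0.007; Fisher p = 0.013.
- *Risk difference.* 0.60 − 0.30 = 0.30, Newcombe 95% interval 0.082 to 0.481.

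The last two chi-squares are equal because the grade mix is the same in both arms. The grade table only spreads the same difference over three degrees of freedom.

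**Example 2: all the extra AEs are mild.** XBYRT 18/4/2, placebo 6/4/2, again 24/40 v 12/40.

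- *Graded participants only.* Grade 2 or above is 6/24 = 25% on XBYRT and 6/12 = 50% on placebo. Chi-square = 0.75 + 1.00 + 0.50 = 2.25 on 2 df, p = 0.32. The arm with twice the incidence looks milder.
- *With a no-AE category* (16/18/4/2 v 28/6/4/2). Chi-square = 3.27 + 6.00 + 0 + 0 = 9.27 on 3 df, p = 0.026.

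**Power for a doubling of incidence.** 20,000 simulated trials per row, 40 per arm, grade mix 60/30/10 in both arms:

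| Incidence | Graded only | With no-AE category | 2x2 incidence |
|---|---|---|---|
| 20% v 40% | 4% | 33% | 50% |
| 25% v 50% | 4% | 47% | 65% |
| 30% v 60% | 5% | 61% | 79% |

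With graded participants only, power stays at about the nominal 5%. With the extra category the test works, but falls 17 to 18 points short of the direct comparison.

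**The case against.** The strongest objection is to a reading that a reader might well infer: that the test leaves out participants with no AE, so a doubling of incidence would show no difference. The article does not support that.

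- **The denominator is unstated, not restricted.** The chi-square sentence compares the two groups and does not limit the table to participants with an AE. The list of grades in Safety monitoring describes a scale, not the rows of an analysis table. With a no-AE row, the results move from p = 1.00 to 0.064 in Example 1 and from 0.32 to 0.026 in Example 2. This stands: p = 1.00 depends on the table layout as well as on the assumed counts.
- **Incidence will be reported.** Secondary outcomes and Statistical analysis agree on this, and 60% v 30% would be plain in the results. This stands too. Descriptive AE reporting is usual in a trial of 80, and the article does not promise a test of incidence.
- **Incidence is compared between arms for the DSMB.** True, but that serves monitoring during recruitment. Three reviews at one per 20 recruited correspond to 3 × 20 = 60 of the 80, if they fall at 20, 40 and 60. It is not the reported final analysis.
- **Table layout belongs in the full protocol or SAP.** Fair for the layout alone. It does not answer the mismatch: the article itself picks the final safety comparison, and picks it on a quantity other than its stated outcome.

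**Conclusion.** The point holds as a minor one. The stated safety outcome is incidence, while the only final between-arm safety comparison named is on grade. That comparison does not respond to incidence if only graded participants enter. If a no-AE category is included, it is less sensitive to a doubling with unchanged grade mix than a direct comparison: p = 0.064 against 0.007 in Example 1, and 33 to 61% power against 50 to 79%.

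It would go too far to say that the trial excludes participants without an AE, that it would miss a doubling of AEs, or that incidence goes unreported. The weakness is confined to the formal comparison.

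The figures rest on assumed AE rates and grade mixes and on 40 analysed per arm. Nor is the grade test worse in every case: where the extra AEs fall in one grade, as in Example 2, a table with a no-AE category also picks up the change in mix (chi-square 9.27, p = 0.026).

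**What to change.** In Statistical analysis, put the between-arm safety comparison on the stated outcome. Give the proportion of participants with at least one AE, at least one grade 3 or higher AE, and at least one SAE. Report each as a risk difference with a 95% score (Newcombe) or exact interval, with all participants in the arm as denominator.

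If severity is also compared, say that the table counts each participant once at the worst grade and keeps participants with no AE as a 'none' category.

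The cost is about two sentences and a little extra analysis. No new data or participants are needed.

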### Randomization, allocation concealment and blinding

Recruited participants will be randomized into the XBYRT or placebo treatment arm by block randomization at a 1:1 ratio, with a block size of 10. The consultant physicians, study team, trial pharmacists and study participants are blinded to the intervention to minimize potential bias. Randomization and blinding will be performed by a third party clinical trial service provider, Singapore Clinical Research Institute, using the sealed envelope method. Participants will collect the granules from the clinical trial pharmacy at NCCS based on their pre-assigned numbers.

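### AE severity is to be compared by a chi-square test over CTCAE grades, which ignores the grade order and leans on sparse cells at 40 per arm; an ordered test plus a separate grade 3 or higher comparison would serve better (minor)

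*Protocol article*

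**What the plan says.** The Statistical analysis section makes two statements about safety. The first is descriptive: "The safety outcomes will be reported in proportions of patients experiencing AEs (% in terms of incidence) using the CTCAE v5.0 Criteria". The second names a test: "Chi-square test will be used to evaluate the difference in severity (by grades) between the XBYRT intervention and placebo groups".

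The Safety monitoring section defines the scale: "There are five grades in ascending order of severity, with grade 1 representing mild symptoms and grade 5 representing death". It also gives the data and safety monitoring board a comparison by arm: "Analysis comparing the incidence of AEs based on the intervention group will be conducted at each DSMB review".

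The Sample size section sets "a total sample size of 80 patients (rounded up from 78), with 40 participants on each arm". This comes from a recommendation of "at least 70 subjects (35 per arm) for estimating the SD for a continuous outcome", raised "to account for a 10% dropout". Allocation is "by block randomization at a 1:1 ratio, with a block size of 10". The size is therefore chosen to estimate a standard deviation, not to detect a difference in safety.

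**The concern.** The article defines an ordered outcome and then names a test that does not use the order. Relabelling the grades at random leaves Pearson's statistic unchanged, so an excess at grade 3 counts no more than an equal imbalance at grade 1. The test spends 4 degrees of freedom on a 2×5 table, or 5 on a 2×6 table with a no-AE category, on what is mainly a one-directional question: are events more severe on the decoction? In addition, the upper grades will probably hold few participants, and the chi-square approximation depends on adequate expected counts.

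At stake is how a non-significant severity result is read. Safety is a stated aim, and the results are meant to inform a larger phase III trial. A test with avoidably low power could make such a result look more reassuring than it is.

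**Working it through.** **1. The plan's own figure.** 70 / (1 − 0.10) = 77.8, which rounds up to 78 and then to 80, or 40 per arm. The stated sample size reproduces and is not in dispute.

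**2. Sparseness.** With 1:1 allocation, a category's expected count in each arm is half its pooled total. An expected count of 5 needs 10 participants in that category: 10/80 = 12.5% at 40 per arm, or 10/70 = 14.3% at 35 per arm. With six categories (none, grades 1 to 5) there are 12 cells. The common rule allows at most 20% of cells below 5. One short category gives 2/12 = 17% and passes; two give 4/12 = 33% and fail. Two of the upper grades each below 12.5% are enough.

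**3. Size and power by simulation.** The documents give no AE rates, significance level or sidedness for safety. All of the following is assumed: two-sided 0.05, one worst grade per participant, empty categories dropped.

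*Set A*: placebo none/G1/G2/G3/G4 = 45/35/14/5/1%, 40 per arm, 20,000 tables per scenario. Expected G3 and G4 counts per arm are 40 × 0.05 = 2.0 and 40 × 0.01 = 0.4. The expected-count rule fails in 99% of tables under no difference. The chi-square rejection rate there is about 3.7%. Power against a proportional-odds shift (repeat runs differ by a point or so):

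| Odds ratio | Chi-square | Linear trend | Loss (points) |
|---|---|---|---|
| 2 | 22% | 37% | 15 |
| 2.5 | 38% | 58% | 20 |
| 3 | 52% | 74% | 22 |

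*Set B*: six categories, 4,000 tables per scenario, 40 per arm. With common AEs (45/33/15/5/1.5/0.5%), power is 19% against 36% at odds ratio 2 and 50% against 73% at 3. With rarer AEs (80% none), it is 36% against 54% at 3 and 63% against 80% at 4. The losses are 17 to 23 points. Under no difference, chi-square rejects in 3.0% (common), 2.3% (rarer) and 1.8% (very rare) of trials. The expected-count rule failed in 92-100% of tables. At 35 per arm the losses are 16 to 24 points.

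**4. Would exact p-values alone repair it?** A permutation version of the unordered chi-square in Set B (1,500 tables, 40 per arm) gives 22%, 55%, 46% and 69% for the same four shifts. It recovers part of the loss but stays below the trend test in each, so much of the loss comes from ignoring order.

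**5. Does the ordered test win against every pattern?** No. Keep Set A's placebo rates, where grade 3 or higher is 6%, and place the excess in the high grades only:

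| Active arm, none/G1/G2/G3/G4 (%) | Chi-square | Trend | Wilcoxon |
|---|---|---|---|
| 45/27/7/18/3 (same incidence) | 35% | 17% | 9% |
| 45/20/14/17/4 (same incidence) | 36% | 25% | 14% |
| 55/15/10/17/3 (lower incidence) | 53% | 9% | 6% |

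**6. A single rare category.** For 5% against 20% at 40 per arm, exact enumeration gives 57% power for uncorrected 2×2 chi-square and 41% for Fisher's test.

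**The case against.** The strongest case for leaving the plan alone has four parts.

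- **The comparison is supplementary.** AE and SAE incidence is the stated safety outcome, and the monitoring board compares incidence by arm at each review. This stands: a reader might infer that the grade test is the trial's only formal safety comparison, but the documents do not support that.
- **The test is not invalid.** A reader might infer invalidity from the sparse cells. The simulated size of about 2-4% is mild conservatism, with no excess of false positives in the scenarios run. Failing a rule of thumb does not in itself make a test invalid.
- **The power gap depends on the alternative.** The proportional-odds shift suits ordered tests. Step 5 shows the reverse when the excess is confined to high grades. A worst-grade score with 0 for no AE mixes incidence with severity. This also stands, and it shapes the fix.
- **Detail belongs in an analysis plan.** The unit of analysis, collapsing of grades and a sparse-cell fallback are commonly left to a plan that is not shown, so their absence is no finding. It would also be speculation to say that the table will count events rather than participants: the severity sentence gives no unit, and the sentence before it counts patients.

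What the objection does not remove is that the article names a specific test and describes the scale as ordered, and the two fit poorly.

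**Conclusion.** The point holds as a minor one. The named test discards the grade order, and its approximation is unreliable for grades with fewer than 10 of 80 participants. Under assumed AE rates it is mildly conservative, and it gives up roughly 15-23 points of power at 40 per arm if the decoction shifts severity upward in general. Those figures rest wholly on assumed grade distributions and a two-sided 5% level.

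It would go too far to conclude that safety signals will be missed. Incidence reporting and review by arm remain. Even the trend test has only about 36-37% power at an odds ratio of 2, so the small sample limits any choice of test. Nor is an ordered test better against every pattern. The primary endpoint is not affected.

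**What to change.** Replace the chi-square sentence with the following content:

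- one record per participant, the worst CTCAE grade, with 0 for no AE;
- arms compared by an ordered test (Wilcoxon or linear trend) with exact or permutation p-values;
- the risk difference with 95% CI for any AE and, separately, for grade 3 or higher.

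The grade 3 or higher comparison must accompany the ordered test, because the ordered test is the weaker one when the excess is confined to high grades and incidence is unchanged or lower. If Fisher's test is used there, the reason is validity in a small table; step 6 shows that it is not a gain in power.

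The cost is about a sentence in the analysis section. No new data are needed, since AEs are already graded and reported by patient. The change should be made before unblinded data are seen.

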### Assessments

Participants will be assessed at four time points: baseline and 4 weeks, 8 weeks and 10 weeks after baseline (Fig. 1). At the baseline visit, the participant’s demographics, medical history, cancer diagnosis and concomitant medications will be recorded in a standardized data collection form. The participants will be assessed for patient-reported outcomes (PRO) and objective blood biomarkers at each time point (Fig. 2). Participants will also be monitored for safety and adverse events (AE).

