### Outcomes

#### Primary outcome

The primary endpoint is the difference in global health status (GHS) score between the XBYRT interventional and placebo arms from baseline to 8 weeks after baseline. The GHS is a two-item domain from the EORTC-QLQ 30.

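### The analysis is called intention-to-treat, but the set it defines is completers without major violations, which is a per-protocol set

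*Protocol article*

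**What the plan says.** All of the defining text is in the protocol article, Statistical analysis. The label comes first: "An intention-to-treat (ITT) analysis approach will be adopted". The same sentence then says what will be analysed: "the data from all participants who are randomized and completed the trial without any major violation of the protocol will be analysed". The sentence after it reads "Missing data will be treated as missing completely at random".

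The section on the primary outcome defines the endpoint: "The primary endpoint is the difference in global health status (GHS) score between the XBYRT interventional and placebo arms from baseline to 8 weeks". Its test is an independent t test at week 8: "The difference in GHS scores at 8 weeks after baseline between XBYRT intervention and placebo will be assessed using independent". Linear mixed models, adjusted for baseline and clinically relevant factors, are also planned for the comparisons over time.

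Two other places bear on the point. Under Assessments, "Participants will be assessed at four time points: baseline and 4 weeks, 8 weeks and 10 weeks after baseline", so follow-up runs two weeks beyond the primary time point. Under Sample size, the total of 80 was set "to account for a 10% dropout".

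For safety, Statistical analysis says "The safety outcomes will be reported in proportions of patients experiencing AEs" and names no separate population. The Secondary outcomes section speaks of adverse events among study participants, with no restriction to completers.

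**The concern.** An intention-to-treat analysis keeps every randomised participant in the arm assigned. The sentence adds two conditions that are only known later: finishing the trial and having no major violation. Either may depend on how a participant tolerated or responded to the granules, and so on the arm. Once people are removed on that basis, the groups compared are no longer the groups that were randomised, and a week 8 difference could partly reflect who was left.

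The primary result would also be reported under a label that it has not earned. An analyst who follows the label and one who follows the definition would analyse different people, and the document does not say which of them is right.

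**Working it through.** **1. The two halves of the sentence, side by side.**

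| Participant | Under the label (ITT) | Under the stated set |
|---|---|---|
| Week 8 score present, major violation | kept | removed |
| Week 8 score present, week 10 missed | kept | removed, if completing means all four visits |
| Left after week 4, week 4 data present | kept, usable in the mixed model | removed |
| Completed, no major violation | kept | kept |

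The halves disagree in three of the four rows. In the first two, the primary score exists and is discarded.

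**2. Does anything else in the plan repair it?** The week 8 t test makes no adjustment for selective loss. The mixed models could use partial records, but the set excludes the people who have them. The missing-completely-at-random statement assumes selective loss away. No other efficacy set is defined.

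**3. The plan's own sample size.** 70/(1 − 0.10) = 77.8, rounded up to 78 and then to 80; this reproduces. At the planned dropout, 80 × 0.90 = 72 remain. The stated set would fall below that by the number of major violators, for whom no rate is given.

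**4. How large could the bias be?** Let f be the share of an arm removed although a week 8 score exists, and D the amount by which those kept outscore those removed. The mean of those kept exceeds the arm's full mean by f × D, so the bias in the treatment difference is

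bias = f(XBYRT) × D(XBYRT) − f(placebo) × D(placebo).

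The document gives neither f nor D. With assumed values, the same D in both arms and no true effect:

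- 10% and 10%, D = 10 or 20: bias 0.
- 15% and 5%: (0.15 − 0.05) × 10 = 1 point, or × 20 = 2 points, towards XBYRT.
- 20% and 0%: 0.20 × 10 = 2 points, or × 20 = 4 points, towards XBYRT.
- 5% and 15%: the same 1 to 2 points, towards placebo.

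For the 15% and 5% case, 40 × 0.85 = 34 and 40 × 0.95 = 38 remain. The standard error is SD × √(1/34 + 1/38) = 0.236 × SD. With a 2-point bias, the two-sided error rate at nominal 5% (normal approximation) is 8.7% for SD 15, 7.1% for SD 20 and 6.3% for SD 25. With a 1-point bias it is 5.9%, 5.5% and 5.3%. The SDs are assumptions too.

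**5. Safety, if the set were applied there.** Assume 12 of 40 participants in an arm have an adverse event (30%). If 4 of them leave because of it, the completers show 8/36 = 22%; if 8 leave, 4/32 = 12.5%. These counts are illustrative only.

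**The case against.** **The wording may be a slip.** The sentence could be a garbled statement of an ITT analysis plus a per-protocol one, and a plan for missing data makes little sense if only completers are analysed. That is plausible, but it confirms that the text cannot stand. The article does not defer the analysis set to another document; it states one.

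**Stopping the granules.** A reader might infer that anyone who stops is excluded. The document does not say so. It defines neither completion nor major violation, asks participants to record missed doses without calling non-adherence a violation, and does not tie visits to adherence.

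**Adverse events.** A reader might infer that people who withdraw because of an adverse event vanish from the safety table. Nothing expressly applies the set to safety. Secondary outcomes refers to study participants, and Safety monitoring has the DSMB compare incidence by arm after every 20 recruited, which fits poorly with a completers-only set. What stands is narrower: only one set is defined, it is worded without limit and follows directly after the safety analysis, so the passages need reconciling.

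**Dropout simulations.** One can simulate 20% against 5% loss driven by poor week 4 scores and find a bias of 0.10 to 0.14 SD. Those participants have no week 8 score, so the t test cannot use them under any set label. That figure measures the missing-data problem and the choice of test, not this sentence, and its 12.5% average loss exceeds the planned 10%.

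**Sample size.** A reader might object that fewer than 70 remain once dropout and violations together pass 12.5% (1 − 70/80). But 70 is a target for estimating an SD, not a power requirement. The relative standard error of a pooled SD, about 1/√(2(n − 2)), is 8.6% at 70 and 9.0% at 64 (20% loss). This adds little.

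**Conclusion.** The contradiction is certain, because it lies inside one sentence and nothing else in the document resolves it. The set described is per-protocol. Taken literally, it discards week 8 scores already collected from major violators and from people who miss only week 10, and it removes early leavers' week 4 data from the mixed models.

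The consequence for the estimate is possible but cannot be sized from the document. It may be zero, or a few GHS points in either direction, depending on who is removed from each arm and how they scored. The illustrations rest entirely on assumed removal rates, score gaps and SDs.

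It would go too far to say that randomisation itself is compromised: allocation and concealment are untouched, and what is lost is the randomised comparison in the analysed data. For safety, the finding is an unresolved inconsistency, not a demonstrated undercount.

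**What to change.** Make these changes in the protocol and the analysis plan, before unblinding:

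1. **Efficacy set.** Include all randomised participants in the arm assigned, using every available assessment regardless of adherence, completion or protocol violation.
2. **Primary analysis.** Take the week 8 GHS contrast from the baseline-adjusted linear mixed model that is already planned. It is valid under missing at random, so someone with week 4 data but no week 8 score contributes. Changing the set alone would not achieve this, because the t test still needs a week 8 score. The missing-completely-at-random statement should go.
3. **Safety set.** Report adverse events in all participants who took at least one dose, and make Statistical analysis and Secondary outcomes agree on this.
4. **Per-protocol set.** Keep completers without a major violation as a sensitivity analysis, and define both terms.

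The cost is a wording change and a little more analysis work. The sample size stays at 80, no visits are added, and the per-protocol result is still reported. Recruitment was still open when the article was submitted.

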#### Assessment of quality of life

The European Organisation for Research and Treatment of Cancer Quality of Life Questionnaire (EORTC-QLQ 30) is a self-administered questionnaire that measures the health-related QOL. The English and Chinese versions of this questionnaire have been validated in Singaporean cancer patients [32, 33]. It consists of 30 items across five functional domains (physical, role, cognitive, emotional and social), three symptom domains (fatigue, pain and nausea/vomiting), six individual items (dyspnea, insomnia, anorexia, diarrhoea, constipation and financial stability) and a global health status domain. All items are linearly transformed into a score ranging from 0 to 100. A higher score represents better functional status and health-related QOL in the functional and global health status domain while a higher score in the symptom domain or individual symptom item is interpreted as a worse extent of symptoms experienced by the patient.

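### The protocol fixes missing completely at random for all missing data and tests week 8 GHS on completers by t test, leaving the primary contrast liable to bias if dropout is outcome-related and differs by arm

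*Protocol article*

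**What the plan says.** Four statements in the protocol article's Statistical analysis section act together.

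- Missingness: "Missing data will be treated as missing completely at random". No exception is made by outcome, visit or arm.
- Primary comparison: "The difference in GHS scores at 8 weeks after baseline between XBYRT intervention and placebo will be assessed using independent *t* test". No covariate and no intermediate visit enters this test.
- Longitudinal analysis: "To assess for the longitudinal effect of score changes over time, linear mixed models will be used to compare the outcomes" between arms at each time point, adjusted for baseline and clinical factors, with random individual effects.
- Analysis set: the approach is called intention-to-treat, but "the data from all participants who are randomized and completed the trial without any major violation of the protocol will be analysed".

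Elsewhere in the article, the Primary outcome section makes GHS the endpoint. The section on quality of life says that the instrument "is a self-administered questionnaire that measures the health-related QOL". The Assessments section sets the visits: "Participants will be assessed at four time points: baseline and 4 weeks, 8 weeks and 10 weeks after baseline". The Sample size section allows for 10% dropout, without reasons or a split by arm.

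**The concern.** Missing completely at random means that whether a week 8 score is missing has nothing to do with the participant's fatigue, quality of life, tolerance of the product or arm. Participants enter with a fatigue score of at least 4 out of 10, take a decoction daily for 8 weeks and rate their own health. Someone who feels worse, or sees no benefit, may well be more likely to leave. The article offers no reason to expect otherwise.

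The assumption is what would justify a t test restricted to those with a week 8 score. If it fails unequally in the two arms, the completers are no longer comparable and the difference in means no longer estimates the effect among those randomised. If the worse-off leave mainly from the XBYRT arm, the error favours XBYRT.

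The trial already collects what a weaker assumption needs: baseline and week 4 GHS, and a planned mixed model. As written, the primary test ignores the earlier scores, and the completer restriction keeps dropouts out of the mixed model too.

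**Working it through.** **Inputs from the protocol article.** Target of 70 evaluable participants (35 per arm), 10% dropout, 80 randomised at 1:1. The article gives no GHS SD, effect size, significance level or dropout by arm, so results are in SD units.

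**The plan's own figure.** 70 / (1 − 0.10) = 77.8, so 78, rounded up to 80. It reproduces and is not in dispute.

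**Step 1: when there is bias.** In one arm, the completers' mean minus the mean of all randomised equals d × g, where d is the dropout share and g is the completers' mean minus the dropouts' mean. Hence

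bias of the contrast = d_X × g_X − d_P × g_P (X = XBYRT, P = placebo).

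With g = 1 SD in both arms:
- 10/10%: 0.10 − 0.10 = 0
- 15/5%: 0.15 − 0.05 = 0.10 SD
- 20/0%: 0.20 − 0 = 0.20 SD

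Dropout that is not completely at random does not by itself bias the contrast. Rates or gaps must differ between arms.

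**Step 2: size with one common mechanism.** Assume that participants leave when a latent normal variable crosses a threshold. It correlates r with the week 4 score, which correlates ρ with week 8. The completers' week 8 mean then shifts by

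r × ρ × k(p), where k(p) = φ(z_p) / (1 − p),

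p is the arm's dropout rate and z_p the matching normal quantile.

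| p | φ(z_p) | k(p) |
|---|---|---|
| 0.05 | 0.1031 | 0.1086 |
| 0.08 | 0.1487 | 0.1616 |
| 0.12 | 0.2000 | 0.2273 |
| 0.15 | 0.2332 | 0.2743 |
| 0.20 | 0.2800 | 0.3500 |

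Assumed ranges: r = 0.5 to 0.9 and ρ = 0.5 to 0.7, so r × ρ = 0.25 to 0.63.

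- 10/10%: difference in k is 0, bias 0.
- 12/8%: 0.2273 − 0.1616 = 0.0657; × 0.25 to 0.63 gives 0.016 to 0.041 SD.
- 15/5%: 0.2743 − 0.1086 = 0.1657; × 0.25 to 0.63 gives 0.041 to 0.104 SD.
- 20/5%: 0.3500 − 0.1086 = 0.2414; at r = 0.9 and ρ = 0.65 (product 0.585), 0.141 SD. This needs a fourfold imbalance and an overall rate of 12.5%, above the planned 10%.

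For scale, the standard error of the contrast at 35 per arm is √(2/35) = 0.24 SD.

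**Step 3: size when the mechanism differs by arm.** Simulation with 40 per arm, true effect 0, visit correlation 0.5 and 6,000 runs per scenario. XBYRT dropout falls with the score (logistic slope −1.5 per SD); placebo dropout is random. The comparator predicts missing week 8 scores by regression on arm, baseline and week 4, and stands in for an analysis valid under missing at random (MAR).

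| Dropout depends on | XBYRT/placebo | t test bias (SD) | t test type I error | MAR-based bias (SD) |
|---|---|---|---|---|
| nothing | 10/10, 15/5, 20/0% | −0.001, 0.003, 0.000 | 4.9, 4.9, 5.7% | −0.001, 0.001, 0.001 |
| week 4 score | 10/10, 15/5, 20/0% | 0.059, 0.091, 0.111 | 5.6, 7.1, 7.3% | −0.002, 0.003, −0.003 |
| week 8 score | 10/10, 15/5, 20/0% | 0.122, 0.177, 0.222 | 8.4, 12.1, 15.6% | 0.083, 0.122, 0.151 |

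The first row, where the true type I error is 5%, shows the simulation noise in those percentages. In the last row, dropout depends on the unseen score itself (missing not at random, MNAR). Using earlier scores then removes only part of the bias.

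**The case against.** **The result need not be biased.** A reader might infer that the week 8 result is biased outright. The documents do not support that: with equal rates and equal completer–dropout gaps the bias cancels, as Step 1 shows. This stands.

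**Adverse-event dropout is supposition.** A reader might also infer that adverse events will drive withdrawal. The article monitors adverse events but never links them to dropout, and gives no reasons or split by arm. This stands.

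**The bias may be small.** With a common mechanism, 12/8% gives at most about 0.04 SD, or 0.8 points if the GHS SD were 20 (an assumption), against a standard error of 0.24 SD. The figure of 0.141 SD needs inputs that the documents do not supply. This stands, and rules out any firm claim about size.

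**A mixed model is already planned and covers week 8.** True, and a likelihood fit to all observed data would need only MAR. But it is not the named week 8 test, and the completer restriction removes that benefit.

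**Details belong in a statistical analysis plan.** The lack of a sensitivity analysis in an article is no fault. The stated assumption is different: it is a rule in the published text, and a later plan could depart from it only by contradicting it.

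**MAR is no cure.** Its near-zero bias in the week 4 row follows from how dropout was simulated, and the week 8 row shows what remains. This stands, and is why the fix includes a sensitivity analysis.

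**Conclusion.** The point holds as a fault in a stated assumption, not as proof of a biased result. For this outcome and population, missing completely at random is needlessly strong, and joined to a completers' t test it leaves the primary contrast unprotected against outcome-related dropout that differs by arm.

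The size cannot be settled from the documents. At 10% overall dropout with one mechanism in both arms it runs from 0 (10/10%) to about 0.10 SD (15/5%, upper end of the assumed correlations). With a mechanism confined to the XBYRT arm, the simulated range is about 0.06 to 0.22 SD. All of this rests on assumed correlations, dropout splits and mechanisms.

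The point is related to, but separate from, the use of the intention-to-treat label for a completers' set: even with that set repaired, a t test would still lose everyone without a week 8 score. The trial's sizing for estimating an SD tempers the consequence but does not remove it, since the article states an efficacy objective on this endpoint.

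**What to change.** Make these changes to the Statistical analysis section together.

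1. Replace the missingness sentence with, for example: *The primary week 8 GHS contrast comes from the linear mixed model fitted by maximum likelihood to all available GHS assessments of all randomised participants, assuming data are missing at random given the observed scores.*
2. Delete the restriction to participants who completed without major violation. Left in place, it would contradict the new sentence and cancel its benefit.
3. Add a sensitivity analysis for MNAR dropout: impute missing week 8 GHS, shift the imputed values by increasing amounts, separately by arm, and report the shift at which the conclusion changes.

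Participants who leave before week 4 have only a baseline score. They contribute to the model only if baseline is one of the modelled assessments rather than just a covariate, so the model text should say which.

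The cost is a little more analysis work and reliance on the mixed-model specification. No extra participants, visits or data are needed, and the sample size stays at 80.
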